2 groups of 75 persons will be formed. One group will have specific education using methodology of learning nests. The other group will be a control group not subject to this specific education. To evaluate, we propose a classical randomized controlled experimental (RCT) design, with randomization at the person-level. For outcome measures, we propose change in HbA1c, increase of social and emotional support and increase of linkage to clinical care. In addition to HbA1c, we propose measuring changes in systolic, diastolic blood pressure, and weight.

**Public health significance :** It is very important to find an education methodology adapted to the African context. This line of diabetes management is essential to improve the management of African diabetic patients.

**Sustainability plan:** If the evaluation of this methodology is conclusive, the Malian state will implement the methodology in the 22 diabetes units of the country.

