### **Methods for the randomization**

The patients will be selected from the list of diabetic patients followed in diabetes consultations of Bamako.

From this numbered list, a selection will be will randomly conducted with a number table to constitute the intervention group. We will verify that all the patients randomly selected to form this group meet the inclusion criteria of the group (see below).

The randomization list will be kept by the principal researchers of the survey.

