### **Inclusion criteria**

- Patients followed in the diabetes units of the project area and doing regular consultations
- Patients with type 2 diabetes or treated or not with insulin
- Poorly controlled diabetes with HbA1c  $\geq 8\%$
- Patients who accepted to undergo the whole process of peer education
- Patients who agreed to perform all biological measures included in the protocol
- Patients aged from 30 to 70 years old

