### **Comparison group**

The group subjected to educations will follow the whole process of peer education described in Part 1 of this Protocol.

The control group will perform these "classic" individual consultations but will not follow the whole process of peer education.

The classical management in diabetes consultations consists of:

- A counselling session
- A measure of blood glucose
- A measurement of blood pressure
- A measure of weight and size
- A complete clinical examination
- A prescription or a renewal of treatment (diabetes pills, insulin, IEC, statins etc ...)

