## Chronogram

|                            | Month 1 - 5 | Month 6       | Month 7                  | Month 8          | Month 9      | Month 10      | Month 11       | Month 12 |
|----------------------------|-------------|---------------|--------------------------|------------------|--------------|---------------|----------------|----------|
|                            | Preparation | Randomization | Pre inclusion
T-X (*) | Inclusion
T 0 | Visit
T 3 | Visite
T 6 | Visite
T 12 |          |
| Identification of patients | ✓           | ✓             |                          |                  |              |               |                |          |
| Patient Education experts  | ✓           |               |                          |                  |              |               |                |          |
| Informed Consent           |             |               | ✓                        |                  |              |               |                |          |
| Clinical examination       |             |               | ✓                        | ✓                | ✓            | ✓             | ✓              |          |
| Laboratory tests           |             |               | ✓                        | ✓                | ✓            | ✓             | ✓              |          |
| Knowledge                  |             |               | ✓                        | ✓                | ✓            | ✓             | ✓              |          |
| Data Processing            |             |               |                          |                  |              |               |                | ✓        |
| Report                     |             |               |                          |                  |              |               |                | ✓        |

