## 6. Potential risks to participants and co

### Risk minimization

The risk of breach of confidentiality and the risks linked to biological tests are minimal, as long as measures are taken to maintain data security and avoid the risk of infections and pain during samplings. To ensure confidentiality, all the study data will be stored separately and the files will be protected by password.

Only people with an obvious need for data access, such as PI, will have the passwords. To strengthen protection measures, data forms will be stored in protected cabinets. It will be important to encode these forms in order to avoid displaying data such as names, addresses, phone numbers and other personal identification data. Only the principal researcher, the co-researchers and the analysts will have access to keys linking the study identifiers to respondents' personal data. The survey forms will be kept for 5 years after the conclusion of the project to enable data validation, and then destroyed.

To minimize the risks associated with the samplings, only new and sterile equipment with disposable needles will be used.

To minimize the risks directly associated with the intervention of peer education, subjects must be fully informed about all aspects of the intervention. This information will be done through an informed consent form. All subjects will be required to sign this declaration of consent as a condition of participation in the study. In order not to exclude the illiterate people, the consent document will be read aloud to all subjects and translated by a translator for people who do not speak French. Subjects will be encouraged to ask questions and will sign the consent only after they have asked all the questions they have.

The participation of subjects will be entirely voluntary. The right of access to medical care will not be affected by the participation or not to this study.

Topics will be able to withdraw at any time.

Before starting the study, the team will have the full receipt of the ethics committee of the Faculty of Medicine, Pharmacy and Dental Medicine in Mali (FMPOS). This receipt will ensure that all commitments will be reviewed, approved and monitored by a national ethics committee. The recruitment of subjects will not begin before the reception of this receipt.

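### Willingness to undergo peer education is checked after random selection and, as described, only in the intervention group, so the education arm may be selected for motivation

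*Supplement*

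**What the plan says.** Four parts of the protocol bear on this point.

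- **Inclusion criteria.** One of the six criteria is "Patients who accepted to undergo the whole process of peer education". It stands in a single common list and names no arm.
- **Comparison group.** Controls receive the usual individual consultations and "will not follow the whole process of peer education".
- **Methods for the randomization.** From a numbered list of clinic patients, "a selection will be will randomly conducted with a number table to constitute the intervention group". The check comes next: "We will verify that all the patients randomly selected to form this group meet the inclusion criteria of the group (see below". The section does not say how the control group is formed, or that its members are checked in the same way.
- **Chronogram.** The columns run "Preparation | Randomization | Pre inclusion", with randomization in month 6 and pre-inclusion in month 7. Informed consent is ticked at pre-inclusion.

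The design is declared as a trial "with randomization at the person-level", and the sample-size section calls it open. The Risk minimization section requires consent of everyone ("All subjects will be required to sign this declaration of consent as a condition of participation in the study") and allows withdrawal ("Topics will be able to withdraw at any time"). The statistical methods section defines no analysis population.

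**The concern.** The criterion concerns something that only one arm receives, and the only eligibility check described falls on that arm after its members are known. Random allocation protects the comparison only if the same patients would have been in the trial whichever arm they were drawn for. Here a patient's answer to the education offer can decide whether they count in the education arm, but it has no stated consequence for a control.

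Patients who are ready to take on a programme of group sessions plausibly also follow diet and treatment advice better. If the unwilling are removed from the education arm alone, part of any HbA1c advantage would reflect who was kept and not what the programme did. This matters for the decision that the trial is meant to serve. The scientific abstract links a conclusive result to adoption in the country's 22 diabetes units, and for that the relevant quantity is the effect of offering peer education to eligible patients.

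**Working it through.** **Step 1: follow one unwilling patient through the plan.** The protocol gives no figure to reproduce on this point, so the first check is a reading of the sections side by side.

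| Stage | Unwilling patient drawn for education | Equally unwilling patient in the control group |
|---|---|---|
| Random selection (month 6) | Drawn from the numbered list | Route into the group not described |
| Check of criteria after selection | Described; the patient fails the acceptance criterion | Not described |
| Consent (month 7) | Required, with the allocation already made | Required, with the allocation already made; no sessions to accept or decline |
| Result | Can be excluded | Stays in |

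The asymmetry needs all three elements: a criterion about the programme, a check after selection described for one group, and consent after randomization. The criterion alone does not produce it. If every candidate were asked before allocation, both arms would be restricted in the same way.

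**Step 2: illustrate the size.** Let *d* be the share of patients drawn for education who are excluded on this criterion. Let *δ* be the amount by which their mean HbA1c change would have been worse than that of the patients kept, whatever the treatment. Assume that the control arm holds the same share *d* of unwilling patients, all retained.

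- Mean change of the whole education arm = mean of those kept + *d* × *δ* (a higher value is worse).
- Analysing only those kept therefore improves the education mean by *d* × *δ*.

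The documents give neither *d* nor *δ*. Both ranges below are assumptions.

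To show the effect on the test, take the SD of 2.0 and the 60 patients per group from the sample-size section. Apply that SD to both arms and use a two-sided 5% normal test; these two choices are also assumptions. The standard error is 2.0 × √(2/60) = 0.365. With no true effect and bias *b* = *d* × *δ*, the chance of a significant result is 1 − Φ(1.96 − *b*/0.365) + Φ(−1.96 − *b*/0.365).

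| *d* | *δ* (points) | Bias *d* × *δ* (points) | Share of the 1-point target | Chance of significance with no true effect |
|---|---|---|---|---|
| 10% | 0.5 | 0.05 | 5% | 5.2% |
| 10% | 1.0 | 0.10 | 10% | 5.9% |
| 20% | 0.5 | 0.10 | 10% | 5.9% |
| 20% | 1.0 | 0.20 | 20% | 8.5% |
| 30% | 0.5 | 0.15 | 15% | 7.0% |
| 30% | 1.0 | 0.30 | 30% | 13.0% |

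The upper *δ* of 1.0 equals the trial's whole target effect, so the last row should be read as a high case.

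**The case against.** The best defence is that the criterion sits in one common list, that all subjects sign the same consent, and that nothing prevents the investigators from asking every candidate before allocation whether they would attend if assigned. Applied in that way, the criterion is balanced between the arms and limits only how far the result generalizes. This is correct as far as it goes. It would be wrong to say that controls cannot meet the criterion, or that the imbalance would persist once the order of consent, eligibility check and allocation was put right. But the protocol does not provide for that order. It describes a check after selection, for the intervention group, with consent later than randomization.

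A reader might also infer that the plan keeps only patients who complete the programme. The documents do not support this. The criterion is acceptance at entry, so a patient who accepted and later missed a session still met it. The right to withdraw applies to all subjects and is not a rule for removing education patients. No section excludes non-attenders. What stands is narrower: with no analysis population defined, their handling is left open.

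Finally, the size in the illustration is simply the product of two assumed numbers. That is true. It shows what would follow from a plausible degree of selection and is not evidence that selection of that degree occurred.

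**Conclusion.** The point holds as one of one-arm selection after allocation. Followed as written, the plan can filter the education arm for willingness without any stated equivalent in controls, and in an open trial the likely direction favours the intervention. That direction is an inference: it rests on willing patients having better HbA1c outcomes regardless of the programme. The size cannot be derived from the documents. On the assumed ranges it is 0.05 to 0.30 points, or 5% to 30% of the 1-point target, and the two-sided error rate rises from 5% to between 5.2% and 13.0%. The source is the acceptance criterion read together with the randomization section and the chronogram, so rewording the criterion alone would not remove the problem.

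**What to change.** Three linked changes:

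1. Replace the acceptance criterion with one that can be asked identically of everyone: *agrees to be allocated to either group, to attend the education sessions if allocated to them, and to have the 0, 3, 6 and 12-month measurements*.
2. In the randomization section and the chronogram, state that this criterion, all other criteria and informed consent are confirmed in every candidate before allocation, and that both groups are formed from the patients so confirmed.
3. In the statistical methods, state that declining or missing sessions after allocation is not a reason for exclusion. Such patients are measured at 12 months and analysed in their allocated group.

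The cost is a reworded criterion, a reordered chronogram and one added sentence on the analysis. Because non-attenders stay in the education arm, the estimated effect may be somewhat smaller, but it will be the effect of offering the programme.

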### **Non-inclusion criteria**

- Diabetic patients not carrying out their monitoring in diabetes units of the intervention area
- Patients followed in the diabetes units of the intervention area but not realizing their consultations regularly
- Patients with type 1 diabetes
- Severe complications within the preceding 3 months: infection, coronary complications, severe renal failure

- Concomitant illnesses threatening the functional or vital prognosis

### **Comparison group**

The group subjected to educations will follow the whole process of peer education described in Part 1 of this Protocol.

The control group will perform these "classic" individual consultations but will not follow the whole process of peer education.

The classical management in diabetes consultations consists of:

- A counselling session
- A measure of blood glucose
- A measurement of blood pressure
- A measure of weight and size
- A complete clinical examination
- A prescription or a renewal of treatment (diabetes pills, insulin, IEC, statins etc ...)

### **Main judgment criteria**

The main judgement criteria on which the analysis will be done to comply with the superiority of the contribution of a group educational approach by the peer will be the evolution of the HbA1c from the inclusion to 1 year:

- the HbA1C gives a reliable reflection of the glycemic control that is not subject to short-term variations or bias caused by the social aspects that may influence self-evaluation of data;
- it responds directly to all practices that peer education aims to change (diet and exercise, self glucose monitoring, proper use of drugs etc ...)
- It is the most important physiological parameter to improve for people with diabetes, as it is related to the probability of occurrence of micro-and macro vascular complications.

For the measurement of glycated hemoglobin, the apparatus used will be the machine "Infopia". The preservation of the reagent throughout the study will be precisely monitored to avoid, with high temperatures, deterioration of reagents and therefore invalid action. The reagents will be stored in reagents storage structures of the laboratories of the health facilities involved. The measures will be undertaken by the laboratory assistants of the structures involved in the project and who will have been beforehand trained.

### **SECONDARY JUDGMENT CRITERIA**

The secondary judgement criteria will be of 2 types:

- Clinical and biological criteria:

- ☐ intermediate evolution of the HbA1c, between 0, 3 months, 6 months and 12 months
- ☐ evolution at T = 0, 3 months, 6 months and 12 months of the systolic and diastolic blood pressure, weight, BMI and waist measurement.

To measure the blood pressure, armbands of different sizes (normal and obese) are available. The adequate armband will be placed on the upper arm and inflated with a manometer, to measure blood pressure using a stethoscope placed in the hollow of the arm on the artery. The systolic and diastolic pressure will be measured. The blood pressure will be measured on the right arm after a rest period of 5 min. The average of the two measurements taken at two minute intervals will be used.

To measure the weight, the scale 'seca' will be placed on a wooden board. As it is not possible to ask the patient to undress, we will estimate the weight of his/her clothes and it will be subtracted from the recorded measurement on the survey form.

To measure the size, a portable measuring apparatus will be installed on a flat surface. Patients must remove their shoes and their chech (headscarf). The legs will be joined and heels placed against the back wall of the apparatus. The patient should stand up straight and look ahead.

All equipment used will be new and in duplicate. This will enable us to ensure a quality control of the measures conformity, comparing the results between the two copies of the same equipment.

The waist measurement will be done with reference methods using a simple tape measure. Clear the abdomen of the client from clothing and accessories. Ask the client to stand up, with feet at the width of shoulder and arms folded across chest without tension. Place one knee on the floor on the right side of the client. The waist is measured at the upper edge of the iliac crest. To locate this bony landmark, palpate the upper part of the right hip until you locate the upper edge of the iliac crest. Mark a horizontal line to mark the midline of the body. Place the ribbon around the waist so that the bottom edge of the ribbon is aligned with the horizontal line. Using the technique of folded arms; superpose the tape held in one hand above the zero shown on the tape held into your other hand. Make sure the ribbon is aligned in a horizontal plane around the waist. Apply enough tension on the ribbon to keep it straight, without pressing into the flesh of the abdomen. At the end of a normal expiration, take the measure to the nearest 5 mm.

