- 3 • Linkage to clinical care: The choice of intervention areas for Mali has been done taking into account the areas where the care of patients is complete with: an effective and operational diabetes consultation, medicines available and a dynamic diabetic patients association. In these areas, the approach is integrated. The addition of the education methodology by the educators will represent another step in the care pyramid of diabetes. All health workers of the area will be involved in the implementing and monitoring of the process. In addition to the role of educator, educators will also be trained to accompany patients in health facilities that manage diabetes in the intervention area. All peer educators will receive a tool representing the circuit of the patient in the intervention area and will give them to each patient during the animations. Finally, after the meetings patients may accompany each other in the health system.

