## CALCULATION OF THE SIZE OF STUDY

In this trial, the patients were randomized into 2 groups:

- Group 1: group educational intervention by peer educators associated with classical management
- Group 2: classical management without peer education

This is a randomized trial comparing open impact on HbA1c of a 1 year peer education compared to a conventional monitoring alone in health centre.

The comparison group is on HbA1c, the primary judgement criteria. The test is a test of superiority. It is assumed that in the reference group, the value of HbA1c is 8.5% and with a **standard deviation of 2.0**, (previous study conducted in the framework of the NGO Santé Diabète Mali under publication) and we consider that the strategy would be interesting if the assessed value of the mean HbA1c decreased by 1 percentage point of HbA1c and the standard deviation of 0.5 .

In this situation, with a risk  $\alpha$  of 5% and a power  $1-\beta$  of 80%, we must include 60 patients in each group.

in order to take into account a proportion up to 20% of patients lost of sight, we decided to recruit 75 patients per group that is to say 150 patients in total.

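### Weight, and hence BMI, is analysed after subtracting an unstandardised estimate of clothing weight in an open trial, which leaves two secondary criteria open to avoidable noise and possible between-arm bias

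*Supplement*

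**What the plan says.** The section on secondary judgment criteria names the outcomes concerned: "evolution at T = 0, 3 months, 6 months and 12 months of the systolic and diastolic blood pressure, weight, BMI and waist measurement". It explains that patients cannot be asked to undress for weighing and then gives the rule: "we will estimate the weight of his/her clothes and it will be subtracted from the recorded measurement on the survey form". It does not say who makes the estimate, by what method, or whether the scale reading and the deduction are kept as separate variables. For height, the same section has shoes and headscarf removed.

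The section on the size of the study describes the design as open: "This is a randomized trial comparing open impact on HbA1c of a 1 year peer education". No section describes blinded measurement. The section on randomization says "The randomization list will be kept by the principal researchers of the survey". On local staff, the item on linkage to clinical care (section 4) says "All health workers of the area will be involved in the implementing and monitoring of the process".

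The safeguard stated for the equipment is "All equipment used will be new and in duplicate", with results compared between the two copies.

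**The concern.** A scale reading is objective. Once an individual judgement is deducted from it, the analysed value is only partly so. Two consequences follow.

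- **Noise.** Each visit's estimate carries its own error. A change from baseline contains two such errors.
- **Possible bias.** Randomization does not protect against an error made after allocation. The sessions deal with food and physical activity, and weight is a listed outcome, so the hoped-for direction is plain to anyone who knows the arm. If deductions in educated patients grew slightly at follow-up relative to baseline, and those in controls did not, the result would look like weight loss from peer education.

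Duplicate scales would not reveal this, because both copies can agree exactly while the deduction is wrong. The other measures are tied down more firmly. Blood pressure has a rest period and the mean of two readings, waist has a bony landmark and a rounding rule, and HbA1c is read by a device operated by trained laboratory staff. Among these, weight is the measure with an explicit discretionary adjustment.

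**Working it through.** **Plan figure to reproduce.** There is none. The protocol gives no SD, target difference or clothing weight for weight or BMI. What follows is an illustration.

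**Inputs from the protocol**
- Evaluable patients: 60 per arm ("we must include 60 patients in each group"). Recruited: 75 per arm, since 60 / (1 - 0.20) = 75.
- Significance level 0.05, from the section on statistical methods. It is taken as two-sided, since the sidedness is not stated.

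**Assumptions not in the documents**
- SD of 12-month weight change: 3 to 6 kg.
- Differential b: 0.2, 0.5 or 1.0 kg. This is the between-arm difference in how the average deduction shifts from baseline to follow-up.
- Height: 1.55 to 1.75 m.

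**Why b is a difference in shifts.** Analysed change = true change + change in actual clothing weight - change in the deduction. A deduction error that is constant over time cancels within the patient, even if its level differs by arm. An error that shifts equally in both arms cancels in the comparison. Only an unequal shift remains.

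**Formulas.** SE = SD × √(2/n). With no true effect, the probability of p < 0.05 is Φ(b/SE - 1.96) + Φ(-b/SE - 1.96).

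**Worked example**, SD 4 kg, n = 60, b = 0.5 kg: SE = 4 × √(2/60) = 0.730; b/SE = 0.685; Φ(-1.275) + Φ(-2.645) ≈ 0.101 + 0.004 = 0.105.

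**False-positive rate, 60 per arm**

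| SD (kg) | SE (kg) | b = 0.2 | b = 0.5 | b = 1.0 |
|---|---|---|---|---|
| 3 | 0.548 | 6.5% | 15.0% | 44.7% |
| 4 | 0.730 | 5.9% | 10.5% | 27.8% |
| 5 | 0.913 | 5.6% | 8.5% | 19.5% |
| 6 | 1.095 | 5.4% | 7.4% | 15.0% |

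With all 75 per arm evaluable, the ranges are 5.5-6.9%, 8.0-17.5% and 17.5-53.2%.

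**BMI.** The shift is b / height². At 1.65 m, 0.5 / 2.7225 = 0.18 and 1.0 / 2.7225 = 0.37 kg/m². Over 1.55 to 1.75 m, the range is 0.16-0.21 for 0.5 kg and 0.33-0.42 for 1.0 kg.

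**Is the arm known when the patient is weighed?** The chronogram places randomization before pre-inclusion and T0, so even the baseline deduction could be made with the arm known. The documents neither state nor exclude this.

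**The case against.** Several stronger readings are tempting, and the documents do not carry them.

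- **That the person weighing guesses and usually knows the arm.** The text names neither the estimator nor the method. The measuring staff are the natural reading, because no reference value is supplied. But the sessions are run by peer educators, the researchers keep the allocation list, and the sentence about local health workers does not say who weighs patients. Knowledge of the arm is plausible in an open trial, but not established.
- **That no analysis could separate the bias from an effect.** The rule can be read as the scale reading being written on the form and the deduction applied afterwards. If so, the raw weight survives and could be analysed. Waist, taken at the same visits after the instruction "Clear the abdomen of the client from clothing and accessories", is also free of the deduction and offers a partial cross-check.
- **That the waist procedure contradicts the reason for not undressing.** Baring the abdomen for a tape measure is compatible with staying dressed for weighing. This is a tension at most.
- **That the bias is about 0.5 to 1.0 kg.** Nothing in the documents supports either value. At 0.2 kg the test stays close to its nominal level.

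It is also fair to say that the deduction has a purpose. If clothing varies much between visits, an accurate estimate could remove some of that variation. The protocol gives no ground for judging its accuracy, and leftover clothing variation is noise, whereas a discretionary deduction can also be directional.

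What stands is that the deduction is unstandardised, that no masking is described, and that the equipment check cannot detect an error in it.

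**Conclusion.** The concern holds as a weakness in the measurement procedure, confined to weight and BMI. The protocol builds an unstandardised estimate into both change scores in an open trial. That brings avoidable noise and leaves room for a between-arm bias if the deduction shifts differently by arm between baseline and follow-up. The documents show that this can happen. They do not show that it is likely or that it would be large.

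The size depends wholly on assumed values: negligible to slight inflation at a 0.2 kg differential, moderate at 0.5 kg and serious at 1.0 kg. The primary HbA1c comparison and the sample size based on it are untouched. The change is worth making because it costs almost nothing and protects two named secondary criteria.

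**What to change.** Replace the sentence on clothing with a rule along these lines:

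*Patients are weighed without shoes and headscarf and, where feasible, in similar light clothing at each visit. The unadjusted scale reading is recorded as its own variable, and the between-arm comparison of change in weight and BMI uses that reading.*

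If a correction is wanted for absolute weight or BMI, add:

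*The deduction is taken from a table by garment type fixed before the first patient, applied identically in both arms and at all visits, and recorded separately from the scale reading.*

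Shoes and headscarf already come off for height, and the rule does not ask anyone to undress, so the stated field constraint is respected.

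The cost is one or two sentences and one extra field on the survey form, plus the table if a correction is kept. The downside is small. Absolute weights will include some clothing, and variation in clothing between visits remains as noise, which is expected to be similar in both arms.
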